## Abstract

**Background:**

Although many musicians perceive music performance anxiety (MPA) as a significant problem, studies about the psychobiological and performance-related concomitants of MPA are limited. Using the biopsychosocial model of challenge and threat as theoretical framework, we aim to investigate whether musicians’ changes in their psychobiological responses and performance quality from a private to a public performance are moderated by their general MPA level. According to the challenge and threat framework, individuals are in a threat state when the perceived demands of a performance situation outweigh the perceived resources, whereas they are in a challenge state when the perceived resources outweigh the perceived demands. The resources-demands differential (resources minus demands) and the cardiovascular challenge-threat index (sum of cardiac output and reverse scored total peripheral resistance) are the main indices of these states. We postulate that the relationship between general MPA level and performance quality is mediated by these challenge and threat measures.

**Methods:**

We will test 100 university music students reporting general MPA levels ranging from low to high. They will perform privately (i.e., without audience) and publicly (i.e., with an audience) on two separate days in counterbalanced order. During each performance session, we will record their cardiovascular and respiratory activity and collect saliva samples and self-reported measures. Measures of primary interest are self-reported anxiety, the resources-demands differential, the cardiovascular challenge-threat index, sigh rate, total respiratory variability, partial pressure of end-tidal carbon dioxide and the salivary biomarkers cortisol, dehydroepiandrosterone, and alpha-amylase. Both, the participants and anonymous experts will evaluate the performance quality from audio recordings.

**Discussion:**

The results of the planned project are expected to contribute to a more comprehensive understanding of the psychobiology of MPA and of the processes that influence musicians’ individual reactions to performance situations. We also anticipate the findings of this project to have important implications for the development and implementation of theory-based interventions aimed at managing musicians’ anxiety and improving performance quality. Thanks to the use of multimethod approaches incorporating psychobiology, it might be possible to better assess the progress and success of interventions and ultimately improve musicians’ chance to have a successful professional career.

**Trial registration:**

Not applicable.

## Background

Music performance anxiety (MPA) has been defined as « the experience of marked and persistent anxious apprehension related to musical performance (…), which is manifested through combinations of affective, cognitive, somatic and behavioral symptoms » [1] , p. 433. MPA is a significant problem for many musicians [2].

Performing publicly can be a psychophysiologically demanding activity for many musicians. Literature agrees that on average, state anxiety is higher before and during a public performance (i.e., in front of an audience or jury) compared to a private performance (i.e., without an audience or jury, e.g., [3, 4]). Compared to private performances, public performances are also characterized by enhanced physiological arousal in most musicians (e.g., [5, 6]). Research on the psychophysiological concomitants of MPA is scant. With regard to their subjective experience, general MPA level has been associated with significant increases in state anxiety from a private to a public performance [3, 7]. Regarding physiological measures, skin conductance, heart rate (HR), urinary adrenaline and noradrenaline did not show significant differences as a function of musicians’ general MPA level [3, 6, 8]. In contrast, analyses of the respiratory responses showed that the general MPA level significantly moderated changes from a private to a public performance in partial pressure of end-tidal carbon dioxide (P_et_CO_2_), total respiratory variability (quantified by the coefficient of variation) and sigh rate [7, 8]. Salivary cortisol (sC), salivary dehydroepiandrosterone (sDHEA), and salivary alpha-amylase (sAA) have yet to be considered in relation to potential MPA-associated differences in the context of music performance. The catabolic hormone cortisol and the anabolic hormone dehydroepiandrosterone (DHEA) are the main products of the hypothalamic-pituitary-adrenal (HPA) axis, a central regulatory system that in most healthy people is activated in response to psychosocial stressors, resulting in increased sC and sDHEA secretion (e.g., [9–12]. Anabolic balance is the ratio of DHEA to cortisol and has been suggested to be a sensitive indicator of well-being and health, more so than cortisol or DHEA alone [11, 13, 14]. Lower anabolic balance is associated with more unfavorable psychological well-being and health outcomes [14, 15]. SAA is an enzyme secreted from the salivary glands that has been increasingly used as a marker of the activity of the sympathoadrenal-medullary (SAM) axis, another important regulatory system involved in the response to psychosocial stressors [16–18]. Researchers have not investigated cardiovascular differences as a function of general MPA level other than for HR and HR variability (HRV) [8].

Not all musicians have the same predisposition when it comes to performing publicly; whereas some thrive, others fail [19, 20]. The general MPA level was shown to be a predictor of more negative self-rated performance among music students performing solo [21]. Few studies have evaluated whether musicians reporting relatively lower and higher general MPA levels differ in their expert-rated performance quality, and findings have been mixed [3, 6, 22]. No study has yet tested simultaneously whether differences in both self-rated and expert-rated performance quality between a private and a public performance vary significantly as a function of musicians’ general MPA level and what mechanisms might explain such effects.

One theoretical framework that offers a potential model to understand individual differences in psychophysiological responses and music performance quality (MPQ) as a function of musicians’ general MPA level is the biopsychosocial model (BPSM) of challenge and threat [23, 24]. This model provides a framework for understanding the motivational processes within the context of motivated performance situations. Motivated performance situations, such as test taking, athletic competitions, and music performances, are situations that require instrumental responses in order to attain valued self-relevant goals [23, 25]. According to the BPSM of challenge and threat, the self-relevance of the task-related goals drives task engagement [25]. Given task engagement, challenge and threat refer to two different states that a person can experience, depending on the balance between her/his subjective evaluations of demands and resources. Challenge occurs when evaluated resources meet or exceed evaluated demands, whereas threat arises when individuals evaluate demands as outweighing available resources. Challenge and threat are understood as labels representing anchors of a single bipolar continuum defined by the resources-demands differential, such that relative differences in challenge and threat (e.g., greater vs. lesser threat) are meaningful [26]. A central tenet of the BPSM of challenge and threat is that challenge and threat can be differentiated by means of specific cardiovascular patterns. The current view is that in the context of motivated performance situations, HR and ventricular contractility (defined as pre-ejection period (PEP) multiplied by − 1; PEP is the time in ms from the initiation of left ventricle contraction to aortic-valve opening) reflect task engagement proximally and goal relevance distally and are common across the challenge-threat continuum. Cardiac output (CO, the amount of liters of blood pumped by the heart per minute) and total peripheral resistance (TPR, an index of net constriction vs. dilation in the vascular system) differentiate challenge and threat. Relatively larger values of the cardiovascular challenge-threat index (CTI), defined as the sum of CO and of reverse scored TPR, reflect relatively greater challenge or lesser threat [24]. Compared to threat, during challenge, arteries are more dilated/less constricted, which facilitates the heart pumping relatively more blood. The cardiovascular pattern of challenge is supposed to be more conducive to approach-related goal pursuit, as blood delivery to the brain and muscles is more efficient [25, 26]. These indices have been extensively validated [23, 27, 28]. The cardiovascular patterns of challenge and threat have been associated with more positive and negative health outcomes, respectively [29–31].

Many studies have shown that individuals exhibiting a cardiovascular challenge pattern prior to cognitive and motor tasks perform better than individuals exhibiting a cardiovascular threat pattern (e.g., [32–35]). Assessing challenge and threat with cardiovascular measures, as opposed to self-reports only, confers advantages because this approach does not rely on individuals’ ability or willingness to accurately report on their experiences, particularly given that nonconscious and irrational influences are affecting them [36, 37]. Furthermore, cardiovascular challenge-threat indices better predict performance than self-reported variables [28, 32, 38, 39], thus further highlighting the usefulness of these physiological parameters. Most studies on the link between challenge/threat states and task performance have used a between-group design. A within-person design can more conclusively show that cardiovascular activity predicts performance quality by excluding the alternative hypothesis that individuals who possess greater ability at a task are more likely to react with a challenge state [28, 40]. Anxious pianists reported lower expectations of being able to complete several tasks relating to piano performance than non-anxious pianists [3], suggesting that increasing levels of MPA might be associated with greater threat/lesser challenge.

The aim of this study is to investigate in university music students (1) whether the differences in their psychophysiological responses and in their MPQ between a private performance and a public performance vary significantly as a function of their general MPA level and (2) whether the cardiovascular CTI and the resources-demands differential are significant mediators of the relationship between the general MPA level and the MPQ. We aim to test the following hypotheses:
*Relationship between general MPA level and challenge-threat*. Higher general MPA level is associated with greater increase in threat from the private to the public performance: With increasing general MPA level, change scores (public minus private) of the cardiovascular CTI and the resources-demands differential (self-rated resources minus self-rated demands) decrease.*Relationship between general MPA level and MPQ.* Higher general MPA level is associated with greater decrease in self-rated and expert-rated MPQ from the private to the public performance: With increasing general MPA level, change scores (public minus private) of self-rated and expert-rated MPQ decrease.*The mediating role of challenge-threat.* The cardiovascular CTI and the resources-demands differential are significant mediators of the relationships between general MPA level and self-rated and expert-rated MPQ.*Relationship between general MPA level and state anxiety.* Higher general MPA level is associated with greater increase in state anxiety from the private to the public performance: With increasing general MPA level, change scores (public minus private) of state anxiety increase.*Relationship between general MPA level and respiration.* Higher general MPA level is associated with greater increase in sigh rate and total respiratory variability and greater decrease in P_et_CO_2_: With increasing general MPA level, change scores (public minus private) of sigh rate and total respiratory variability increase, whereas change scores of P_et_CO_2_ decrease.*Relationship between general MPA level and salivary measures of HPA axis activity and SAM axis activity.* Higher general MPA level is associated with greater increase in sC and greater decrease in sDHEA, anabolic balance and sAA: With increasing general MPA level, change scores (public minus private) of sC increase, whereas change scores of sDHEA, anabolic balance and sAA decrease.

## Methods/design

### Participants

Participants will be university music students recruited from university music schools by means of electronic invitations and posting on social media. Based on sample size estimations (see chapter Sample size calculation), we aim to collect complete data from 100 students.

Participants will have to be students in the department of classical music, between 18 and 35 years of age and in general good health. Exclusion criteria are cardiovascular, neurologic, respiratory and endocrine diseases, and the use of drugs with effects on the cardiovascular, nervous, respiratory and endocrine systems, including recreational drugs, beta-blockers and anxiolytic medication. Individuals wearing a pacemaker and working night shifts will also be excluded. A current diagnosis of panic disorder or eating disorders are additional exclusion criteria. Women will be excluded if they are pregnant or lactating. Eligibility to participate will be determined with an entry online questionnaire. Participants will receive 250 Swiss Francs as compensation if they complete all phases of the study protocol.

### Study protocol

Participation in the study consists of completing an entry online questionnaire, attending three laboratory sessions (Habituation session, Performance session 1, Performance session 2) and completing a final online questionnaire (Fig. 1). The study is conducted in French or English depending on participants’ preference.

**Fig. 1 Fig1:**
[figure not shown]
Study protocol

### Entry online questionnaire

In the entry online questionnaire, we will collect sociodemographic, academic, music and health-related data as well as the students’ general MPA level. Eligible participants will be contacted to arrange three appointments (Habituation session, Performance session 1, and Performance session 2). The two performance sessions will be scheduled ensuring that the participants have no other public performances neither on the same day of the performance session, nor the day before, or after it.

### Habituation session

Participants will be tested individually. Upon arrival to the lab, the experimenter will explain the study protocol to the participant and obtain written consent. This will be followed by the measurement of participant’s body height and weight, which are used to compute the body mass index (BMI). Afterwards, the participant will be familiarized with the physiological measurements. The experimenter will show the different instruments and explain their function. Afterwards, the sensors of the four devices Finometer, VU-AMS, BioRadio and Capnostream will be applied, and the participant will be asked to sit for 8 min alone. After removing the sensors of the Finometer and the Capnostream, the participant will be invited to play his/her instrument for a few minutes. Information about the comfort level regarding the sensors during the two periods will be obtained, and adjustments to the sensors will be made if required. The participant will also be familiarized with the saliva sampling procedure.

In the second part of the habituation session, the participant will be presented with a list of instrument specific music pieces from which he/she will have to choose one to perform during the following performance sessions. The pieces belong to the standard repertoire usually required for auditions, competitions and exams. The duration of the pieces is between 3 min and 4 min and 30 s (e.g., first 4 min of the solo parts of the clarinet concerto in A major, K. 622 by W.A. Mozart). We will provide the participants with the exact number of bars to perform and require them to perform the selected pieces by heart and without accompaniment during the two performance sessions. Participants will be given up to 2 days to choose their music piece. Finally, the experimenter will give the participant the following information about the upcoming performance sessions: the session order (private before public session or vice versa) and the audience composition (composed of the experimenter and five to seven music connoisseurs including two experts who will rate their MPQ). The experimenter will also explain the MPQ Scale to them.

### Private and public performance sessions

One month after the habituation session, the participant will come to our laboratory for the two performance sessions. For each participant, the two sessions will take place 2 days apart (e.g., Monday and Wednesday) at the same time of the day. Participants will be scheduled at either 1 pm or 3.45 pm. The procedures of the two sessions are identical, except for the fact that the participants will perform without audience in the private session and in front of an audience of six to eight persons in the public session. Participants are randomly assigned to one of the two possible orders. The procedure of a performance session is shown in Fig. 2.

**Fig. 2 Fig2:**
[figure not shown]
Performance session procedure – (Q = Questionnaire; S = Salivary sample) The quiet sitting periods correspond to a period where the participants are sitting alone at a table and required to keep their hands on the table, keep their eyes open, stay quiet and still and not cross their legs. Q1 consists of questions assessing participants’ compliance with the behavioral instructions (food intake, etc.) Q2 includes the questionnaires CSAI-2R (cognitive anxiety, somatic anxiety, self-confidence), self-reported demands and resources, STAI-6 and SAMq. Q3 includes the questionnaires FSS-2, MPQ Scale, CSAI-2R (somatic anxiety), self-reported demands and resources, STAI-6 and SAMq. Q4 and Q5 include the questionnaires CSAI-2R (somatic anxiety), STAI-6 and SAMq. Q6 includes the questionnaires CSAI-2R (somatic anxiety), STAI-6, SAMq, Post-Music Performance Thoughts Questionnaire, a question about performance engagement and a question about practice time.

The day before each performance session, the participants will receive an electronic reminder in which they are asked to comply with the following requirements: no alcohol intake and no intense physical activity 24 h before the visit, no heavy meal 1h15min before the visit, no caffeine intake (including coffee, tea or chocolate) 1h15min before the visit, no cigarettes or any products containing nicotine 1 h before the visit, and no food intake 15 min before the visit. The email for the public performance session will also remind the participants of the audience composition.

First, participants will be given 5 min to prepare their instrument and warm up. Then, they will fill in a first questionnaire (Q1) to verify their compliance with the behavioral instructions (food intake, etc.). After attaching the sensors of the Finometer, VU-AMS, BioRadio and Capnostream and performing the required checks and calibrations, a first saliva sample (S1) will be collected followed by an 8-min period during which the participants will be sitting alone at a table and required to keep their hands on the table, keep their eyes open, stay quiet and still and not cross their legs. Afterwards, participants will fill in a second questionnaire (Q2) and take a second saliva sample (S2). Following the removal of the sensors of the Finometer and of the Capnostream, the participants will perform their music piece. After the performance, the participants will fill in a third questionnaire (Q3) and take a third saliva sample (S3). The rest of the session will consist of three 5-min sitting periods each followed by questionnaires (Q4, Q5, Q6) and saliva collection (S4, S5, S6). The timing of the sitting periods, performance, questionnaires, and saliva collection, as well as the content of each questionnaire are given in Fig. 2.

Performances will be recorded with a handy recorder Zoom H4 (Zoom North America, Hauppauge, NY, USA) placed on a tripod close to the participant. It will be combined with a microphone DPA 4099 (DPA Microphones, Inc., Longmont, CO, USA), which will be placed on the participant’s instrument with a clip or on a music stand depending on participant’s preferences (only on a music stand for singers). Audio recording will be started and stopped by the experimenter while participants are completing questionnaire Q2 and Q3, respectively.

### Final online questionnaire

One week after completing the second performance session, participants will receive the recordings of their two performances via an e-mail containing a link to a final online questionnaire and a Dropbox link to two mp3 audio files named “Recording1” for the first performance session and “Recording2” for the second performance session. In the online questionnaire, participants will be asked to listen to these audio files in the same order and rate the MPQ using the MPQ Scale.

Finally, the participant will fill in questionnaires assessing their trait anxiety, social anxiety and depressive symptoms, all of which are potential confounding variables because they can affect the psychophysiological measures.

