##### *Social anxiety*

Social anxiety will be assessed with the self-reported version of the Liebowitz Social Anxiety Scale (for English version [75, 76], for French version [77]). This scale quantifies fear and avoidance of social interaction situations (12 items, e.g., “Calling someone you do not know very well”) and performance situations (12 items, e.g., “Acting, performing or giving a talk in front of an audience”) during the last week. The possible responses for experienced fear are 0 (none), 1 (mild), 2 (moderate), or 3 (severe), and the possible responses for avoidance behavior are 0 (never), 1 (occasionally), 2 (often), or 3 (usually). The total score can range from 0 to 144 with higher scores indicating greater social anxiety. The test possesses good psychometric properties [78]*.*

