##### *Depressive symptoms*

Depressive symptoms will be assessed with the Beck Depression Inventory-II (for English version [79], for French version [80]). This inventory is a unipolar questionnaire assessing depressive symptoms during the last 2 weeks with 21 items. Each item contains four sentences, which are coded from 0 (less close to depression, e.g., “I do not feel sad”) to 3 (*closest to depression*, e.g., “I am so sad or unhappy that I can’t stand it”). The total score can range from 0 to 63 with higher scores indicating more severe depressive symptoms. The test has good psychometric properties [79].

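### Three intended control variables (trait anxiety, social anxiety, depressive symptoms) are measured only after both performances and their re-hearing, so sensitivity analyses adjusted for them cannot separate confounding from consequence

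*Protocol article*

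**What the plan says.** The section Final online questionnaire sets the order. The e-mail comes first: "One week after completing the second performance session, participants will receive the recordings of their two performances via an e-mail". Next, "participants will be asked to listen to these audio files in the same order and rate the MPQ using the MPQ Scale". The three scales come last: "Finally, the participant will fill in questionnaires assessing their trait anxiety, social anxiety and depressive symptoms, all of which are potential confounding variables". The reason given there is that they can influence the psychophysiological measures.

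The scales differ in the period they ask about. Depressive symptoms: "This inventory is a unipolar questionnaire assessing depressive symptoms during the last 2 weeks with 21 items". Social anxiety is asked for "during the last week", and 12 of its 24 situations are performance situations. Trait anxiety has no stated period and uses a habitual-frequency response format.

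General MPA, the exposure, is taken in the entry questionnaire, more than a month before the performance sessions. Neither the entry measures nor the questionnaires of the performance sessions (legend of Fig. 2) include any of the three scales.

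Data-analytic strategy names session, general MPA level and their interaction as the main predictors. It lists the three scores among the possible control variables for sensitivity analyses. A control is added if it makes theoretical sense and shows a significant association with the outcome.

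**The concern.** The article treats the three scales as causes of the responses but measures them after the responses, after the performance, and after the participant has heard and graded it again. A student whose public performance went badly, and who has just been reminded of it, might score higher on depression or social anxiety for that reason. The score would then partly be a result of the outcome it is meant to adjust.

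What is at stake is the meaning of the sensitivity analyses. If the MPA slope shrinks after adjustment, a reader would want to conclude that general anxiety or low mood explained part of it. With late measurement, the same shrinkage could come from adjusting for a consequence. The selection rule adds to this, because a scale that moved with the outcome is more likely to pass a test of association with it. An analysis plan cannot repair this once the data are in, since no pre-session values would exist.

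**Working it through.** The point disputes no figure in the article. The check covers dates first, then what late measurement can do to an adjusted slope.

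**Dates.** Inputs: the form is sent 7 days after session 2 (Final online questionnaire); "the two sessions will take place 2 days apart" (Private and public performance sessions); recall is 14 days for depressive symptoms and 7 days for social anxiety (their own sections). No completion deadline is given, so let d be the delay in days between receipt and answer (assumed).

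When the form is answered, session 2 lies 7 + d days back and session 1 lies 7 + 2 + d = 9 + d days back. A session is inside a window of W days if its distance is at most W.

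- Depressive symptoms, W = 14: session 1 needs 9 + d ≤ 14, so d ≤ 5; session 2 needs 7 + d ≤ 14, so d ≤ 7. Both sessions are covered for d = 0 to 5, only session 2 for d = 6 or 7, neither after that.
- Social anxiety, W = 7: session 1 needs 9 + d ≤ 7, which never holds; session 2 needs 7 + d ≤ 7, so only d = 0, at the edge of the window. The re-hearing and grading fall inside the window if done in the same sitting.
- Trait anxiety: no stated window, so no date check applies.

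**Adjusted slope (illustration; all values assumed).** Let M be general MPA and Y the public-minus-private change in an outcome where higher is better, both standardised, with true slope b = -0.25. Let T be the pre-session value of a scale, correlated ρ with M and with no effect of its own on Y. The late measurement is C = T + gY, where g is the feedback from outcome to score. Regressing Y on M and C gives

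- coefficient of C: k = g(1 − b²) / [(1 − ρ²) + g²(1 − b²)]
- coefficient of M: b − k(ρ + gb)

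Example with ρ = 0.5 and g = -0.2: 1 − b² = 0.9375; k = -0.1875 / (0.75 + 0.0375) = -0.1875 / 0.7875 = -0.238; ρ + gb = 0.5 + 0.05 = 0.55; the slope of M is -0.25 + 0.238 × 0.55 = -0.119.

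| ρ | g = 0 | g = -0.1 | g = -0.2 | g = -0.3 |
|---|---|---|---|---|
| 0.3 | -0.250 | -0.217 | -0.181 | -0.144 |
| 0.5 | -0.250 | -0.185 | -0.119 | -0.056 |
| 0.7 | -0.250 | -0.119 | +0.007 | +0.117 |

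A simulation with 1,000,000 draws per cell agrees to within 0.003. Adjusting for T itself, the pre-session value, returns -0.25 throughout.

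**Selection rule.** In this model the scale has no effect on the outcome, so k = 0 when g = 0. With feedback, k moves away from zero (-0.238 in the example). A rule that keeps controls associated with the outcome is therefore more likely to keep a scale because it reacted.

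**The case against.** The case on the other side has several parts, and much of it stands.

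- A reader might infer that all the recall windows cover the sessions. They do not: this is true of the depression scale alone, and only for answers within 5 days of receipt.
- A reader might infer that the main results are biased. The documents do not support this, because the main models contain session, general MPA and their interaction, and the three scores enter only sensitivity analyses.
- A confounder must act before the outcome, but it need not be measured before it. A stable trait recorded later can stand in for its earlier value. This is most convincing for trait anxiety.
- The article calls these variables confounders of psychophysiological measures, and the focal cardiovascular and respiratory period is the 8-minute sitting period before playing. Participants do not re-hear their cardiac output or cortisol, so any route from those measures to the later scales is indirect. However, Data-analytic strategy does not limit the controls to physiological outcomes. The concern is strongest for self-rated performance quality, which participants grade just before the scales.
- A reader might infer that participants lost before the final form would leave gaps in the control data. The article largely meets this by recruiting until 100 participants have complete data and by paying only those who complete all phases.
- Feedback from one short performance to these scores is possible but not shown.

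What remains is that no pre-session value of any of the three scales is planned, so the adjusted analyses have no means of ruling feedback out.

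**Conclusion.** The point holds within limits. It concerns the sensitivity analyses that adjust for these three scores, chiefly for self-rated performance quality and chiefly with the depression and social anxiety scores. Those analyses could not distinguish removed confounding from over-adjustment, and the outcome-significance rule makes the choice of an affected scale more likely. Other listed controls recorded before the sessions, such as age, gender, BMI and academic year, are not touched.

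The size cannot be derived from the article, which gives neither the correlation of the scales with general MPA nor any effect of performing on them. The tabulated range, -0.22 to +0.12 against a true -0.25, rests on assumed correlations of 0.3 to 0.7 and feedback of -0.1 to -0.3. It shows what could happen and is not an estimate. With zero feedback there is no bias. The change is worth making because it is cheap and only possible before data collection.

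**What to change.** Collect the three scales once, online, between the habituation session and the first performance session, and keep the final questionnaire for the audio self-rating. Time the depression scale late in that month, so that its 2-week window lies close to the sessions but ends before them. A form filled in much earlier would miss symptoms near the physiological recordings.

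If the schedule cannot change, describe results adjusted for these scales as conditioning on post-outcome measures, and choose the control variables on prior grounds instead of by their significance with the outcome.

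The cost is a small amendment to the questionnaire schedule, with the same instruments and the same total burden. The downsides are a slightly longer pre-session load and some possible priming, which the month between habituation and performance limits less the later the form is completed.
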